## Abstract

**Background:**

Family caregivers of individuals with spinal cord injury (fcSCI) provide assistance with activities of daily living for individuals with spinal cord injury (SCI), which can include emotional support and physical assistance. Over time, providing daily support can put fcSCI at risk of experiencing caregiver burden. This burden can have a substantial impact on fcSCI’s well-being. A direct predictor of the fcSCI burden is their appraisal of their ability to cope with the individual with SCI. Therefore, supporting fcSCI’s access to education relevant to their role and the health and well-being of the individual with SCI can help decrease this burden.

**Objective:**

The purpose of this study is to evaluate the fidelity of the COMPANION intervention and its study protocol designed to improve outcomes for fcSCI.

**Methods:**

Recruitment began in June 2024 and is ongoing. Data collection was completed in April 2025. The fcSCI randomized into the intervention group have been given access to COMPANION after randomization. Data collection for both participant groups (COMPANION and control) will be performed after randomization and will be performed again after 3 months (T2) and 6 months (T3) to capture the impact of COMPANION on fcSCI’s psychological well-being.

**Results:**

As of June 2024, recruitment has begun and is ongoing. Data collection has begun and will conclude in 2025. The fcSCI randomized into the intervention group have been given access to COMPANION after randomization. Data collection for both participant groups (COMPANION and control) is collected after randomization, and again after three months (T2) and six months (T3) to capture the impact of COMPANION on fcSCI’s psychological wellbeing.

**Conclusions:**

Study results will evaluate whether the full study can and should be conducted and will lead to the refinement of COMPANION.

**Trial Registration:**

ClinicalTrials.gov NCT06364813; https://clinicaltrials.gov/study/NCT06364813

**International Registered Report Identifier (IRRID):**

DERR1-10.2196/67709

## Introduction

### Background

Approximately 360,000 individuals have spinal cord injury (SCI) in the United States [1] and a further 86,000 in Canada [2]. SCI causes substantial disruption in the patient’s life habits, routines, and level of independence. In many cases, individuals with SCI need considerable human assistance to perform any activities that exceed their motor and sensory capability [3]. Family caregivers (defined as “any relative, partner, friend or neighbor who has a significant personal relationship with, and provides a broad range of assistance for, an older person or an adult with a chronic or disabling condition” [4]) of individuals with SCI (fcSCI) often provide the majority of physical care to their family members with SCI [5]. Furthermore, individuals with SCI may experience higher levels of depression and anxiety and lower levels of life satisfaction than the general population [6]; therefore, fcSCI may also provide emotional support, alongside physical support. Providing physical and emotional care and support can have a substantial impact on fcSCI’s physical and psychological well-being [5]. Many fcSCI report physical, emotional, and financial challenges associated with their caregiving roles and tend to neglect their own mental and physical health [7-9]. Over time, these experiences put fcSCI at high risk of burnout from an increased caregiver burden, which is associated with decreased well-being [5,8].

Caregiver burden is defined as “the extent to which caregivers perceive that caregiving has had an adverse effect on their emotional, social, financial, physical or spiritual functioning” [10]. Previous research indicates that 40%-46% of fcSCI report moderate-to-severe levels of caregiver burden due to the long-term nature of the injury and the caregiver role [10]. The burden associated with caregiving also influences fcSCI’s ability to respond to the needs of individuals with SCI, and the long-term impact of caregiving demands on fcSCI may result in decreased support and quality of care for individuals with SCI. Hence, attending to risk factors and interventions that target the well-being of fcSCI is crucial.

Although family caregivers of individuals with other chronic conditions, especially dementia, receive considerable attention in research [11-13], the development and evaluation of interventions that address the unique challenges faced by fcSCI have received less attention. The informal caregiving integrative model [14] describes several factors that determine caregiver burnout, which can be divided into 3 main categories: (1) caregivers, that is, caregivers’ sociodemographic characteristics, psychological factors (eg, emotion regulation, perceived competence), and physical state; (2) caregiving setting, that is, primary stressors (eg, living with the care recipient, being a spouse) and secondary stressors (eg, having a reduced social life, loss of friends); and (3) social environment, that is, informal and partner support, professional support (eg, availability of professional support and relationship with health care providers), and sociocultural environment (eg, how the caregiving role is perceived in society). Although some of the factors impacting the caregiver burden cannot be modified (eg, gender or relationship), other factors, such as emotion regulation or relationships with health care providers, are modifiable. Specifically, the informal caregiving integrative model [14] explains that fcSCI’s appraisal of their ability to cope with individuals with SCI is a direct predictor of their burden. The fcSCI’s coping appraisal is directly associated with their need for available resources and knowledge regarding the health condition of individuals with SCI. Therefore, helping fcSCI access education can increase their appraisal of their coping ability and lower levels of the caregiver burden.

A recent scoping review by McKay et al [15] suggested that fcSCI maintain better well-being if they have enough leisure activities, strong problem-solving skills, and practical and emotional support. In a recent qualitative study of Canadian fcSCI, Jeyathevan et al [16] identified that access to community and social support, a better relationship with individuals with SCI, and mastery in caregiving could help fcSCI provide sustainable care for individuals with SCI and for themselves. Although the findings of Jeyathevan et al [16] identified several critical needs of fcSCI, few studies have investigated the impact of different types of interventions on outcomes for family caregivers’; the studies that have been conducted have focused mainly on teaching problem-solving skills [16-20]. Additionally, even though rehabilitation facilities invite fcSCI to join educational sessions, these sessions primarily focus on patients’ needs. Compounding this challenge, fcSCI often have limited time, making attendance at in-person sessions difficult.

### Objectives

In our objective to improve outcomes for fcSCI, this study will evaluate the implementation fidelity of an innovative intervention program for health education with an online approach (eHealth) that aims to improve the well-being of fcSCI. COMPANION, cocreated with caregiver partners and health care professionals, is an interactive eHealth education program that is based on adult learning principles [21] and a user-centered approach [22]. The goal of COMPANION is to address fcSCI’s specific challenges in caring for themselves and for individuals with SCI and facilitate the provision of accessible online education. We envision COMPANION will improve access to existing knowledge for fcSCI and individuals with SCI and provide customized (eg, developed through understanding caregivers’ perspective), interactive (eg, quizzes), and engaging eHealth education (eg, new educational videos and audios) in the form of online modules, which are essential aspects of an eHealth tool [23], to better prepare and support fcSCI for providing care for themselves and individuals with SCI.

## Methods

### Study Design

This paper provides the details of a study protocol for a concurrent mixed methods study, including a feasibility randomized controlled trial (RCT). The study is registered with ClinicalTrials (NCT06364813). The purpose of the feasibility RCT is to (1) assess the fidelity of the process, resource, management, and treatment indicators and (2) estimate the parameters needed for a large-scale, multisite RCT [24]. Secondary objectives will be to assess the effect of COMPANION on primary and secondary clinical outcomes for fcSCI [24,25].

To assess the feasibility and intervention fidelity of COMPANION, a 6-month feasibility RCT with a 1:1 allocation ratio will be conducted, comparing COMPANION with the standard education and resources available to fcSCI. The study will incorporate quantitative and qualitative design methods administered through surveys and a final exit interview. In conjunction with RCTs in rehabilitation, the use of qualitative methods has been recommended to spot unexpected variables and findings [26,27]. The interview will be an opportunity for participants to share perspectives about their experience using COMPANION, with findings used to interpret clinical outcomes and, when integrated with quantitative findings, identify patterns and paradoxes between the results.

### Ethical Considerations

The University of British Columbia Research Ethics Board has approved this study (approval number H20-01461). All participants will sign the informed consent form prior to responding to baseline measures. To protect participants’ identity, all identifying materials will be removed from the data files. This includes Qualtrics information, such as IP addresses and participant contact information. A master list containing the participants’ names will be created, and each participant will be given a unique study number. The study numbers will be used to identify participants. The master list will be kept separate, password-protected, encrypted, and filed away from the participant data. Consent forms will be kept in a separate password-protected folder. The semistructured interviews conducted 6 months after baseline (T3) will be transcribed verbatim, and identifiable information will be removed prior to beginning analysis. All participants will receive CA $50 (US $37) after completing each timepoint.

### Study Timeline

The following 3 data collection timepoints will be used in the feasibility RCT: the time immediately following successful screening of the participants, during which baseline data will be collected and access to COMPANION will be provided to participants in the intervention group; 3 months after baseline data collection (T2); and 6 months after baseline data collection (T3). Please see Multimedia Appendix 1 for further information about the study timeline.

As of June 2024, recruitment and data collection for the study began and are ongoing. All data collection is performed via a secure online survey tool available through our institute (Qualtrics). After successful screening, randomization, and baseline data collection have been conducted, participants will be asked to complete the baseline survey. Follow-up data will be collected at 3 months (T2) and 6 months (T3). At baseline-T3, participants will respond to measures that assess primary (subjective burden) and secondary (objective burden, relationship quality satisfaction, distress, physical and mental health, and caregiving competence) outcomes. The purpose of baseline is to collect baseline information about the outcomes of the study. The purpose of T2 is to capture the influence of the intervention on our psychological outcomes of interest (eg, depression, anxiety, stress, and competence). T3 reflects the optimal change period for self-reporting of physical outcomes (eg, physical health and functioning).

### Sample Size and Inclusion and Exclusion Criteria

Suggested sample sizes for a feasibility RCT range from 12 to 30 per experimental group [28,29]. We aim to recruit at least 20 participants per group. Inclusion criteria for participants are, at the time of recruitment, as follows:

Family caregiver of an adult individual with SCI (similar to previous studies of this population [30,31]; in this study,family caregiveris defined as an individual who is primarily responsible for providing immediate informal daily care for a relative with SCI).Age >18 years.Living with the individual with SCI in the community.Living in North America.SCI of the patient has not happened within the previous 6 months.

Those fcSCI who had major medical and physical conditions that require routine visits to medical doctors (eg, cancer) will be excluded from the study, in addition to fcSCI providing care to individuals with SCI who are still patients in a rehabilitation facility.

### Recruitment

The fcSCI are approached to participate (1) indirectly by sending letter and email invitations to previous patients or research participants of our center (GF Strong Rehabilitation Center and the International Collaboration on Repair Discoveries [ICORD]) and asking them to invite their family caregivers to contact us and (2) directly by asking our caregiver partners, Wives and Girlfriends of Spinal Cord Injury, to approach their members (approximately 6000 members mainly in North America) and invite them to participate in this study. We used social media advertisements to facilitate recruitment. Participants are recruited internationally from locations across North America. To include the participation of individuals from remote and rural areas, all participants are invited to participate digitally through a virtual meeting platform. In-person participation is not offered regardless of physical proximity to the research team.

### Randomization and Masking

Upon successful enrollment and baseline data collection, participants are randomized by the research staff using the online service Sealed Envelope [32] with a block size that is undisclosed to the study manager. The research staff is responsible for randomization and the delivery of the intervention, while the study manager, who is responsible for enrolling participants and conducting data collection, remains masked to the participants’ group allocation. To mitigate performance bias, participants are instructed not to discuss their program or group allocation with any member of the research team, except the research staff, and both the study manager and research staff will continue to reinforce this point when contacting participants. The research staff is responsible for receiving emails from participants and removing information related to group allocation before forwarding participant emails to the study manager.

### Intervention

COMPANION was designed through a collaboration between researchers, health care providers, and family caregivers (end users and stakeholders) using the Technology Co-Design Model [33,34]. The current preliminary version of COMPANION consists of 8 self-paced online modules, which can be accessed remotely from any location.

### Intervention Group

Participants in the intervention group are able to choose the order in which they complete the COMPANION modules and are encouraged to complete them all. They are also encouraged to invite individuals with SCI to view the COMPANION materials with them, as several of the modules include exercises that the participants can do with individuals with SCI and information regarding processes that the fcSCI can navigate with individuals with SCI (eg, changes in their relationship, considerations for hiring a home care aide, and accessing financial and legal support). Participants receive the web address, instructions to access the website using personalized encrypted login information, and guidelines on how to use the program. Modules have been designed so they can be stopped at any point, with progress automatically saved. Module formats include embedded video clips, voiceovers, and additional resources, including links to other available information. As topics are introduced in the course, participants are reminded that the content in the modules is not a substitution for expert professional advice and are instructed to consult with their health care providers, when needed. If participants have questions regarding the content of the modules, they can submit their questions to the research staff, who will review the submitted questions and, if necessary, forward them to one of the experts on the expert panel comprising a selected team of professionals who have experience working with individuals with SCI and their family caregivers. The selected expert will provide additional resources or information to address the participants’ questions. The experts on the proposed project will not provide personal interventions to family caregivers; instead, they will focus on providing information to address the submitted questions only. Questions submitted by participants during the feasibility study will be used to modify and improve COMPANION. The research team will record participants’ submitted questions and the amount of time spent addressing each question and responding to participants. This information will also be used to further improve and modify COMPANION.

In the first 3 months of enrollment of participants in the intervention group in this feasibility RCT, the research staff remotely monitor online analytics (eg, login frequency, module progression) of COMPANION and contact a participant if no online activity is noted in a 2-week period in order to promote use and troubleshoot potential technical problems.

### Control Group

Control group participants will receive the usual care available at their local rehabilitation clinic. Immediately upon reaching the 6-month timepoint, control group participants will be given access to the current version of COMPANION.

### Feasibility Indicators

The RCT’s primary feasibility indicators will be used to address the COMPANION intervention’s design and fidelity by assessing process issues, resource issues, management issues, and treatment issues. See Table 1 for further information about the feasibility indicators.

**Table 1 table1:** Feasibility indicators.

Feasibility indicator and components		Subindicator	Expectation
**Process**			
	Recruitment rate	Number of participants recruited, number of women and men recruited	Mean of 3-4 participants/month: total of 40
	Consent rate	Percentage of participants consenting	<10% participant refusal
	Retention rate	Percentage of participants with T3^a^ data	Complete data collection for >80%
	Perceived benefit	Responses to the SUS^b^, qualitative interviews at T3	>85% of responses strongly agree/agree, qualitative analysis informing clinical importance
	Assessor masking	Percentage unaware of group status	100% of participants not unmasking their treatment
**Resources**			
	Treatment adherence (COMPANION)	Completed all the modules	>85% of participants
	Data collection: participant and evaluator burden	Baseline, T2^c^, and T3	>85% of participants to complete in ≤2 hours, >85% of participants to complete in ≤1.5 hours
	Expert burden	Time (minutes) spent in answering participants’ questions and following up with them	Mean time spent per participant <2 hours for baseline and <1 hour for T2, <20% phone calls back for clarification
**Management**			
	Internet stability	Downtime due to technical or mechanical issues	>90% of participants not without internet for >2 days
	Participant processing time	Time from data collection to treatment	Mean time <10 days at each site
	Treatment administration issues	Posttreatment evaluation form (study educator)	Any issues identified modifiable without substantial changes to the protocol
**Treatment**			
	Dose level response	Correlation between training time and change score	A positive correlation

^a^T3: 6 months after baseline.

^b^SUS: System Usability Scale.

^c^T2: 3 months after baseline.

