#### Subjective Burden

The primary clinical outcome (ie, caregiver burden) will be measured through the survey using the Zarit Burden Interview [35. Studies have demonstrated a direct association between the caregiver burden and the quality of life for family caregivers [19]. As family caregivers’ appraisal of their ability to cope with their family members’ health condition is a direct predictor of their burden [14], and COMPANION aims to provide the required education and information for fcSCI so that they perceive and experience less challenges in providing care, we have selected fcSCI’s subjective burden as our primary clinical outcome. The short 12-item version of the Zarit Burden Interview will be used to assess the subjective burden [35]. The fcSCI are asked to use a 5-point scale (from 0=never to 4=nearly always) to evaluate how often they experience certain feelings. Total scores can range from a minimum of 0 to a maximum of 48. A total score ranging between 0 and 10 indicates no-to-mild burden, 10-20 indicates a mild-to-moderate burden, and >20 indicates a high burden. This measure has been considered as valid and reliable (Cronbach α=.78) among fcSCI [36].

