#### Objective Burden

The survey will be used to administer several secondary clinical outcome measures. The first secondary outcome will be measured using the 38-item Dutch Objective Burden Inventory assessing fcSCI’s objective burden [37]. Each questionnaire item lists a specific caregiving activity that corresponds to 1 of the following 4 domains: personal care (eg, helping with eating and drinking), practical support (eg, buying groceries), motivational support (eg, motivating to quit or reduce smoking), and emotional support (eg, showing understanding). The fcSCI are asked to rate their perceived burden for each task over the past 3 months using a 3-point scale (1=not at all burdensome, 2=somewhat burdensome, 3=very burdensome). Total scores are calculated as the average of all individual answer scores, ranging from 1 to 3. A higher total score indicates a higher objective burden. Testing of the measure has affirmed adequate validity and reliability among Dutch and Canadian caregivers [38,39].

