#### Feasibility

Feasibility outcomes will be treated as binary based on the expectations, as shown in Table 1. Specific objectives will be evaluated as a “success,” indicating that no major adaptation of the protocol is needed before proceeding with a definitive RCT, or “revise,” indicating changes must be made before continuing with the definitive RCT.

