## Discussion

### Summary

This study aims to investigate the feasibility of the COMPANION eHealth protocol. COMPANION e-Health modules have been developed to provide the education needed for family caregivers of individuals with SCI. By providing the necessary education, we aim to reduce the caregiver burden and improve caregivers’ overall well-being. Health education using online approaches has been lauded for being interactive and enabling learners to engage over sustained periods. Benefits of eHealth can include improving the quality of care [37,64,65], enhancing communication between health care users and providers [66], reducing costs [67], and increasing access to evidence-based health information. As the COMPANION modules were designed specifically to address aspects of caregiving that are significant to fcSCI, COMPANION has the potential to increase fcSCI’s knowledge and health literacy around challenges that they face when providing care (eg, emotional challenges, challenges in conducting medical tasks, challenges with isolation and accessing social support). By providing access to education and resources regarding factors that are known to mitigate the caregiver burden for fcSCI, such as social support [68] and coping appraisal [14], COMPANION may be used to impact fcSCI’s overall feelings of a burden, quality of life, and well-being. Findings from conducting the feasibility RCT that evaluate the feasibility and acceptability of our study procedures can be used to inform the design of a definitive RCT assessing the effectiveness and impact of COMPANION on clinical outcomes compared to usual care pursued by fcSCI. Conducting a definitive RCT can further contribute meaningfully to family caregiver research and literature about mitigating the burden experienced by caregivers of individuals with SCI.

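### The dose-response indicator passes on any positive correlation with an undefined change score, so its sign has no fixed meaning and a pass is about a coin toss when use and change are unrelated

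*Protocol article*

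**What the plan says.** The Treatment block of Table 1 (Feasibility Indicators) has one row, dose level response. Its subindicator is "Correlation between training time and change score" and its expectation is "A positive correlation". The Feasibility paragraph under Data Analysis then states: "Feasibility outcomes will be treated as binary based on the expectations, as shown in Table 1". Each objective is labelled either *success* (no major adaptation before the definitive trial) or *revise* (changes needed first).

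Under Subjective Burden the authors write "we have selected fcSCI’s subjective burden as our primary clinical outcome". It is measured with the 12-item Zarit Burden Interview, scored 0 to 48, "and >20 indicates a high burden". The Discussion summary gives the intended direction: "we aim to reduce the caregiver burden and improve caregivers’ overall well-being".

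The Statistical Analysis paragraph adds that usage data will be summarised descriptively to evaluate dose level response and adherence. It does not define the change score.

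**The concern.** A criterion based on the sign of a correlation needs a defined outcome and a defined direction of change. Table 1 gives neither, yet it fixes the sign and attaches a label to it. Two problems follow.

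First, the same data can earn either label, depending on how change is coded. This matters most for the primary outcome, where the hoped-for movement is downward.

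Second, the threshold is zero. Even with the coding settled, a positive r in one small arm is weak evidence of a dose-response. At stake is the label on the only Treatment row, which is meant to help decide whether COMPANION or its protocol needs changing before a definitive trial. If the definition is chosen after the correlations have been seen, the label loses what meaning it has.

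**Working it through.** The plan attaches no sample size, power or alpha to this criterion, so there is no figure to reproduce. The check has three steps.

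**Step 1. Direction of each scale, from the outcome sections.**

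| Outcome | Higher score means | Sign of r(time, follow-up − baseline) if more use brings benefit |
|---|---|---|
| Zarit (primary) | worse | negative |
| Objective burden ("A higher total score indicates a higher objective burden") | worse | negative |
| DASS-21 | worse | negative |
| CIIQ costs | worse | negative |
| DAS-32 | better | positive |
| VR-12 | better | positive |
| CCS | better | positive |

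One unqualified positive sign cannot mean benefit on raw change scores across this set.

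**Step 2. Effect of the coding.** By identity,

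r(time, follow-up − baseline) = −r(time, baseline − follow-up).

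Any non-zero correlation therefore passes under one coding and fails under the other. In one simulated arm of 20 in which more use lowers burden, r = −0.58 with follow-up minus baseline (*revise*) and r = +0.58 with baseline minus follow-up (*success*).

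**Step 3. How often r > 0 occurs.** Controls receive COMPANION only after month 6, so training time exists only in the intervention arm. Inputs:

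- n = 20, the planned minimum per group (Sample Size section).
- n = 27, which is 54/2, assuming an even split of the 54 enrolled (Results).
- True correlations ρ of ±0.3, which are illustrative and not taken from the article.
- Bivariate normal data.

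The Fisher z approximation is P(r > 0) ≈ Φ(atanh(ρ) × √(n − 3)). For ρ = −0.3, atanh(ρ) = −0.3095:

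- n = 20: Φ(−0.3095 × √17) = Φ(−1.276) = 0.101
- n = 27: Φ(−0.3095 × √24) = Φ(−1.516) = 0.065

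Simulation with 100,000 replicates per setting gives:

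| True ρ | n = 20 | n = 27 |
|---|---|---|
| −0.3 | 0.093 | 0.061 |
| 0 | 0.50 | 0.50 |
| +0.3 | 0.908 | 0.939 |

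The ρ = 0 row is the same whichever way change is coded. The other two rows swap meaning with the coding. If change is follow-up minus baseline on the Zarit, ρ = −0.3 is the beneficial case and passes only 6% to 9% of the time. If change is improvement, ρ = +0.3 is the beneficial case and passes 91% to 94% of the time.

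The 95% limits for r around zero are ±tanh(1.96/√(n − 3)):

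- n = 20: tanh(1.96/√17) = tanh(0.475) = 0.44
- n = 27: tanh(1.96/√24) = tanh(0.400) = 0.38

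Even under the favourable coding at n = 20, a pass is only 0.908/0.50 = 1.8 times as likely with a true correlation of 0.3 as with none.

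**The case against.** The strongest reply is that Table 1 never says the change score is the Zarit's, nor that it is follow-up minus baseline. In a row headed dose level response, a positive correlation reads naturally as more use, more improvement, and that fits the authors' stated aim. Which outcome, which interval and which subtraction are details that an article may leave to a fuller document. The row is also one of 12 components, no stated rule lets it decide progression alone, and the effect on burden is examined separately by group at each timepoint.

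Much of this stands. A reader might infer that the criterion simply has the wrong sign, so that harm is scored as success and a working programme is sent back for revision more than nine times in ten. The article does not support that. It needs two assumptions the text does not make, the Zarit as the outcome and follow-up-minus-baseline coding, plus an assumed correlation of −0.3. Nothing ties the row to the Zarit either: caregiving competence, where higher is better, would be a defensible choice for an education programme.

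The reply does not remove the rest. The article states the pass rule itself, with its sign, and takes the binary label from Table 1. A threshold of zero is weak under every reading. Describing usage data does not change that while the row is still scored pass or fail.

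**Conclusion.** The indicator is badly fixed. Its sign has no single meaning across outcomes scored in opposite directions. For the primary outcome it is right if change means improvement and reversed if change means follow-up minus baseline, and the article does not say which.

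The finding that does not depend on coding is that the rule is met about half the time when training time and change are unrelated. Values of r up to about 0.44 in either direction (n = 20), or 0.38 (n = 27), are compatible with no association. A pass therefore cannot support a *success* label. These figures assume roughly bivariate normal data and complete follow-up in the arm; the 27 also assumes an even split. Losses to follow-up would widen the limits.

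Severity is moderate. One feasibility label of 12 is affected, and the randomised comparison of burden is not.

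**What to change.** Amend the dose level response row before analysis starts. The article reports data collection complete in April 2025 and analysis expected from June 2025, so the definition could still be set before results are seen.

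- Name the outcome, for example the primary Zarit score, and the interval, baseline to T2 or baseline to T3.
- Define change so that positive means improvement: baseline minus follow-up for the Zarit, objective burden, DASS-21 and CIIQ; follow-up minus baseline for CCS, DAS-32 and VR-12.
- Replace the sign-only pass or fail with r and its 95% confidence interval, described as a non-randomised association within the COMPANION arm, since participants largely determine their own training time.

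The cost is one table row and a line of code, with no new data. The downside is that the row, and with it the Treatment block, no longer yields a simple *success* or *revise* label.
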